### Outcomes

Primary and secondary outcomes will be accessed at baseline, after 12 weeks (end of intervention) and 24 weeks (Table 4).

**Table 4 Tab4:** Primary and secondary outcomes for the participants of the study

	Measurement	Baseline (T0)	Post 12 week of Intervention (T1)	12 weeks of follow-up (T2)
***Primary outcomes***	Plasma levels of inflammatory cytokines	x	x	x
	Function of leukocytes in the peripheral circulation	x	x	x
***Secondary outcomes***	Short Physical Performance Battery	x	x	x
	Maximal isometric handgrip strength (kg.f)	x	x	x
	Gait speed (m/s)	x	x	x
	Fatigue	x	x	x
	Geriatric depression Scale (GDS)	x	x	x
	Dual-task_gait + verbal_ (m/s)	x	x	x
	Quality of Life (EQ-5D)	x	x	x
	FRAIL-BR	x	x	x
	SARC-F	x	x	x
	Physical activity frequency during follow-up			x

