#### Primary outcomes

The primary outcome measure is a change in the inflammatory profile after a 12-week multicomponent physical exercise program (VIVIFRAIL©), whether a reduction in inflammatory mediators in serum (IL-6, TNF- α, IL1beta, IL-17, IL-22, and CXCL-8) or culture supernatants (IL-6, TNF- α, IFN-gamma and IL-17) or an increased production of anti-inflammatory mediators (IL1RA and, IL-27) in serum or IL-10 and IL-4 in culture supernatants. We hypothesize that the intervention would lead to an anti-inflammatory profile.

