#### Secondary outcomes

Secondary outcomes are a change in: (1) physical performance according to the SPPB, (2) handgrip strength, (3) fatigue according to specific items of the CES-D scale, (4) gait speed, (5) dual-task gait speed, (6) depressive symptoms, (8) FRAIL and SARC-F scores, and (7) quality of life.

We hypothesize that the intervention group could present at least a 1-point increase in the SPPB, better measurements of strength and gait speed, less referred fatigue and depressive symptoms, and better quality of life.

All the participants will be coded using numbers and the data will be stored electronically. After storage, data will be checked by a second researcher to ensure data quality*.* All participant information will be stored in areas with limited access. All records that contain names or other personal identifiers will be stored separately from study records identified by code number.

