### Statistical analyses

First, sample calculation was based in a previously published results from a clinical trial of resistive physical intervention among frail older adults [31]. This study is similar to our design and outcomes. In this trial, outcomes involved inflammatory biomarkers. To date, VIVIFRAIL trials were done in inpatients and nursing home patients and without inflammatory biomarkers as outcome measurement. For a 30% reduction in IL-6 with 80% power and a 5% error, we would have 18 older adults in each group for 12 weeks. Assuming a drop out until 25% within this period, the groups should be composed of 22 elder adults each.

Statistical analyzes will be performed using the SPSS program (version 23.0; SPSS, Inc., USA) and R version 3.6.2. Initially, the Shapiro Wilk and Levene tests will be used to test the distribution and homogeneity of the data. Descriptive analysis will be performed and the means and standard deviation of the variables with normal distribution will be presented, and the median and maximum and minimum values ​​for the non-normal variables and 95% confidence intervals.

Analysis by intention to treat will be performed. A sensitivity analysis will be performed for missing data, through multiple imputation. To compare the variables between the groups, the Student t-test will be used or the Mann-Whitney test for non-parametric variables. To assess the difference between the moments of intervention, one-way analysis of variance (ANOVA-oneway) with repeated measures or the Friedman test for nonparametric variables will be used.

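### The only named comparison between arms is not adjusted for baseline and leaves open whether 12-week values or changes are tested

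*Protocol article*

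**What the plan says.** The Statistical analyses section assigns one task to each of two families of tests.

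- Between arms: "To compare the variables between the groups, the Student t-test will be used or the Mann-Whitney test for non-parametric variables". No covariate is named, and the variables are not defined as 12-week values or as changes.
- Over time, the relevant sentence opens: "To assess the difference between the moments of intervention, one-way analysis of variance (ANOVA-oneway) with repeated measures or the Friedman test for nonparametric variables will". As worded, this has no arm factor and no arm-by-time term.

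The outcome sections speak of change. Under Primary outcomes: "The primary outcome measure is a change in the inflammatory profile after a 12-week multicomponent physical exercise program". Under Secondary outcomes: "Secondary outcomes are a change in: (1) physical performance according to the SPPB", followed by the remaining measures.

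The Outcomes section sets the measurement times: "Primary and secondary outcomes will be accessed at baseline, after 12 weeks (end of intervention) and 24 weeks". Table 4 marks both primary outcomes at T0, and every secondary outcome except one: "Physical activity frequency during follow-up" is marked at T2 only.

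The sizing statement is: "For a 30% reduction in IL-6 with 80% power and a 5% error, we would have 18 older adults in each group for 12 weeks". After the dropout allowance, each group has 22. Randomization and blinding gives 22 per arm in each of three frailty states, 66 against 66 overall.

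**The concern.** Baseline is collected for almost every outcome, and outcomes are described as changes, yet the named arm comparison is a plain two-sample test. Two analyses fit the wording.

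- **12-week values.** T0 is left out. An arm that starts higher by chance tends to finish higher, and that carries into the estimated effect.
- **Changes from T0.** T0 is used, but with its coefficient fixed at 1. When r is below 1 and the spread is similar at both visits, this subtracts too much. An arm that starts higher by chance then tends to show a larger fall.

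The two readings can give different estimates and p-values from the same data, with chance imbalance acting in opposite directions. With 18 to 22 per arm in each frailty state, precision is scarce, and the plan gives up some that its own measurements could supply. Because the article fixes the test by name, this is a stated choice, not a detail left to another document.

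**Working it through.** **Inputs from the article (Statistical analyses; Randomization and blinding).** 18 evaluable per group, 80% power, 5% error; 22 per arm per frailty state; 66 per arm overall.

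**Assumptions.** Two-sided 5% (the article does not state sidedness). Equal SD at T0 and 12 weeks. r between 0.3 and 0.8 (not in the article).

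**Step 1: the plan's own figure.** No SD is given, so 18 cannot be derived forwards. Solving the two-sample t-test backwards for 18 per group, 80% power and two-sided 5% gives a standardised difference d = 0.961. The normal approximation gives (1.960 + 0.842) × √(2/18) = 0.934.

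**Step 2: relative variance of the estimated arm difference.**

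- 12-week values: 1
- Changes: 2(1 − r)
- ANCOVA: 1 − r²

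ANCOVA against 12-week values is 1 − r². ANCOVA against changes is (1 − r²) / [2(1 − r)] = (1 + r)/2. Both are below 1 for any r strictly between 0 and 1. Changes are less precise than 12-week values when r < 0.5.

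**Step 3: power at 18 per group, if 18 was sized on 12-week values.** Noncentral t with effect d, d/√[2(1 − r)] and d/√(1 − r²); 34, 34 and 33 degrees of freedom.

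| r | 12-week values | Changes | ANCOVA |
|---|---|---|---|
| 0.3 | 80% | 66% | 83.5% |
| 0.5 | 80% | 80% | 90% |
| 0.7 | 80% | 95% | 97% |

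**Step 4: power at 18 per group, if 18 was sized on changes.** The test on changes has 80% by construction. The ANCOVA effect is d × √[2/(1 + r)].

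| r | Changes | ANCOVA |
|---|---|---|
| 0.5 | 80% | 90% |
| 0.7 | 80% | 86% |
| 0.8 | 80% | 84% |

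The gain grows with r in step 3 and shrinks with r in step 4.

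**Step 5: small-sample allowance.** The ANCOVA figures use the large-sample variance. Estimating the T0 slope inflates it on average by 1 + 1/(2 × 18 − 4) = 1.03, which lowers power by roughly one percentage point at r = 0.3 to 0.5. Against 12-week values, ANCOVA then gains when (1 − r²) × 1.03 < 1, that is r above about 0.17. Against changes, it gains when 1.03 × (1 + r)/2 < 1, that is r below about 0.94.

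**Step 6: chance imbalance at T0.** The SD of the arm difference is √(2/n) in SD units:

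- 22 per arm: √(2/22) = 0.30; a difference above 0.5 SD occurs in about 10% of randomisations.
- 66 per arm: √(2/66) = 0.17; a difference above 0.5 SD occurs in about 0.4%.

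Given a 0.5 SD imbalance, 12-week values shift by 0.5 × r and changes by 0.5 × (r − 1). At r = 0.3, 0.5 and 0.7 that is +0.15, +0.25 and +0.35 SD for 12-week values, and −0.35, −0.25 and −0.15 SD for changes. ANCOVA shifts by 0 on average.

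**The case against.** A reader might infer that the plan ignores baseline altogether. The article does not support that. Primary and secondary outcomes are defined as changes, and if changes are what is tested, T0 is already in the analysis. The fault is then lost efficiency and an unstated choice, and at r = 0.8 the variance saving is only 10%, since (1 + 0.8)/2 = 0.90.

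A reader might also infer that the planned test is biased. It is not: imbalance under randomisation is random error, the standard error already allows for it, and averaged over randomisations the t-test stays valid. Lost precision and carried-over imbalance are largely two views of the same thing and should not be counted twice.

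The size of the gain is also uncertain. The article states neither the sidedness nor the variable behind the 18, and gives no r. A one-sided 5% test would imply d of about 0.83 (normal approximation). The article does not say that arms are compared within each frailty state, although sizing at 22 per group points that way. If states are pooled, chance imbalance is much smaller.

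Finally, an article may leave covariates to an analysis plan. That does not dispose of the point: the article names the test, and no adjusted arm comparison appears beside it. These objections limit the claim and its size. They do not remove it, because ANCOVA comes out ahead under both readings and both sizing assumptions, except at the extremes of r in step 5.

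**Conclusion.** The point holds as one of efficiency and clarity, not validity. The only named arm comparison is unadjusted, and the article does not say what it is applied to. Baseline adjustment would raise power from 80% to somewhere between about 83% and 97% over the correlations considered, depending on r and on which variable the 18 was sized for. These figures assume a two-sided 5% level, equal SDs at the two visits and 18 evaluable per group. The imbalance figure of 0.30 SD applies if arms are compared within frailty state, and 0.17 SD if states are pooled. The change is worth making because the T0 data are already scheduled and the revision also settles which variable is tested.

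**What to change.** In Statistical analyses, replace the sentence on between-group comparison with the following specification:

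- **Continuous outcomes with a T0 value:** the primary arm comparison is an ANCOVA of the 12-week value on arm and the participant's own T0 value, adding frailty state if the three states are pooled. The same model is used at 24 weeks.
- **Cytokines:** log-transform both the T0 and follow-up values, and report the ratio of geometric means with a 95% CI. A 30% reduction corresponds to a ratio of 0.70.
- **Fatigue, if analysed as present or absent:** logistic model with arm and T0 status.
- **Physical activity frequency during follow-up:** compare arms without baseline adjustment, as there is no T0 value.
- **t-test or Mann-Whitney test:** keep as supportive, stating whether it is run on 12-week values or changes.

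Cost: one degree of freedom per model for the T0 covariate, two more if three frailty states are pooled, and slightly more analysis work. No new visits, samples or participants are needed.

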Few controversial studies investigated the effect of exercise on inflammatory biomarkers in frailty. A stabilization of IL-6 and CRP was observed in frail and pre-frail older persons during physical training and nutritional support, while controls presented an increase in these cytokines [12]. Moreover, those who improved physical performance lowered IL-6 levels. In another study, a resistance training for knee flexors and extensors muscles did not influence low-grade inflammation in older adults. However, plasma levels of TNF type 1 receptors were inversely related to the muscle strength at the end of 12-weeks [13]. In youngers, the increase in the serum level of TNF-α after intervention correlated with reductions in muscle mass after a 4-week follow-up period, suggesting that TNF-α may play a role in muscle loss due to detraining [14]. Collectively, these studies show the potential anti-inflammatory role of physical activity.

Thus, this single-center parallel randomized controlled trial will allow to investigate whether a low-cost multicomponent exercise program called VIVIFRAIL© [15, 16] has benefits for reducing inflammation and improve the functional status among older persons with different frailty status. This program is performed according to the functional capacity and has been demonstrated to be a safe and effective to reverse the functional decline associated with acute hospitalization in seniors [17, 18]. The specific objectives of this RCT will be evaluate the effectiveness of the VIVIFRAIL© [15, 19] program with respect to the concentration of inflammatory and anti-inflammatory mediators and in the functional status of older persons in the different frailty status during 12-weeks. It is hypothesized that older persons submitted to the VIVIFRAIL© exercise protocol will present a decrease in serum levels of pro-inflammatory interleukins, associated with an increase in serum levels of anti-inflammatory interleukins and, secondarily, an improvement in the functional status is expected.

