- Low level of physical activity: Low physical activity is defined as spending less than 383 cal per day for males and 270 cal for females, corresponding to the lowest quintile of energy expenditure in the older population. The energy expenditure will be measured with some items of the Minnesota Leisure Activity Questionnaire, which has been translated and validated in Portuguese [22]. Based on self-report frequency and duration of physical activities (including sports and leisure activities), the calculation of caloric expenditure will be performed by multiplying the metabolic equivalent of the task (MET) of each activity by the body weight (Kg), time (minute) and the predetermined measure of 0.0175.

After evaluating the Frailty Physical Phenotype criteria, participants who have 1–2 of these components will be considered as pre-frail, 3 or more components as frail, and those without any as robust.

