#### Inflammation

The peripheral blood of all participants will be collected. From everyone, approximately 9 mL of blood will be collected in tubes containing clot activator and 9 mL in tubes containing sodium heparin for peripheral blood mononuclear cells (PBMCs) and polymorphonuclear cells (PMNs) isolation. The serum will be separated after clot formation by centrifugation at 1200 *g* for 15 min at room temperature, then the serum will be collected, aliquoted and immediately stored at 20 °C. The cytokine measurement will be performed using ELISA with specific commercial kits for IL-6, TNF- α, IL1beta, IL-17, IL-22, CXCL-8, IL1RA, and IL-27 (R&D Systems and Biolegend manufacturers’ instructions).

PBMCs will be isolated using Ficoll-Hypaque density gradient centrifugation (density 1.077 - Pharmacia Biotech, Piscataway, NJ, USA). After removing PBMCs, the buff-coat cells (containing PMNs) will be collected and diluted in fresh RPMI medium and submitted to new centrifugation over a Ficoll-Hypaque solution at a density of 1.119). After separation, PBMCs and PMNs will be resuspended (2 × 10^6^ cells/mL) in RPMI medium supplemented with fetal bovine serum (10%), L-glutamine, sodium pyruvate and gentamicin (RPMI-S) and distributed in 24-well plates. Cultures will be maintained without additional stimulation or stimulated with ultrapure LPS (100 ng/mL - Invivogen) and PMA (100 ng/mL - Sigma) for PMNs and with ultrapure LPS (100 ng/mL - Invivogen) and PHA (10 mg/mL) for PBMCs. The cells will be kept for 24 h, at 37 °C in a CO_2_ incubator (5%). After the culture period, the supernatant will be collected and stored at − 80 °C and will be evaluated by ELISA with commercial kits for each cytokine (IL-10, IL-4, IFN-gamma, IL-17, TNF- α, IL-6) (R&D Systems and Biolegend).

The details of the pro-inflammatory and anti-inflammatory mediators investigated in this study are presented in the Table 2.

**Table 2 Tab2:** Pro-inflammatory and anti-inflammatory mediators

Mediator	Major Cellular Sources	Major Activities
**IFN-gamma**	Th1 cells, NK cells	Activation of inflammatory macrophages (M1), inhibition of Th2 responses, induction of leukocyte migration.
**IL-1beta**	Monocyte/macrophages, PMNs.	Synthesis of acute-phase proteins by hepatocytes, induction of local and systemic inflammatory effects.
**IL-1RA**	Monocyte/macrophages, dendritic cells.	Specific inhibitor of IL-1alpha and IL-1beta by competition with the cellular receptor.

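### The only test of change over time has a visit factor and no arm factor, and no stated test is fixed on the between-arm difference in 12-week change

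*Protocol article*

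**What the plan says.** The Statistical analyses section of the protocol article names two families of test and gives each a job.

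- Groups: "To compare the variables between the groups, the Student t-test will be used or the Mann-Whitney test for non-parametric variables". No time point, change score or baseline adjustment is attached.
- Visits: "To assess the difference between the moments of intervention, one-way analysis of variance (ANOVA-oneway) with repeated measures or the Friedman test" for nonparametric variables. This is the only longitudinal test. No arm-by-visit term or model of change by arm appears anywhere in the article.

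The outcomes are changes. Under Primary outcomes: "The primary outcome measure is a change in the inflammatory profile after a 12-week multicomponent physical exercise program". The secondary outcomes are likewise listed as changes.

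The hypotheses describe what happens to exercisers and state no contrast with control. In the Background, those who exercise "will present a decrease in serum levels of pro-inflammatory interleukins"; under Secondary outcomes, "the intervention group could present at least a 1-point increase in the SPPB".

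Frailty status is assigned from baseline components, with "3 or more components as frail, and those without any as robust". Three of the five components return as outcomes: "2) handgrip strength, (3) fatigue according to specific items of the CES-D scale, (4) gait speed".

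**The concern.** A one-way repeated-measures ANOVA, or its rank counterpart, asks whether the mean differs between T0, T1 and T2 in one set of people. Run within an arm or with arms pooled, it contains no exercise-versus-control contrast and so makes no use of the randomisation. Anything that moves both arms alike, such as assay or storage drift, season or retest familiarity, counts as a difference between visits.

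For grip, gait speed and fatigue there is a further source. Participants are sorted into frailty groups by their T0 readings on these measures, so people classed as frail will on average look somewhat better at the next reading without any treatment. Cytokine levels play no part in forming the groups, so for the primary outcome the issue is shared drift.

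The stake is the trial's main conclusion. Outcomes defined as change, hypotheses worded as change in exercisers, and a longitudinal test confined to visits together leave room for a within-arm P-value to be taken as the result. The protocol fixes no between-arm contrast that would take precedence.

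**Working it through.** The plan gives no figure for the behaviour of this test, so there is nothing to reproduce. The check has four steps.

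**1. Inputs.**
- From the document: three visits (baseline, 12 and 24 weeks); 18 evaluable participants per group (Statistical analyses); 1:1 allocation (Randomization and blinding).
- Assumed, because the document gives no values: equal correlation ρ of 0.5 or 0.7 between visits; unit SD; a shift of δ = 0.25, 0.5 or 0.75 SD, identical in both arms, at T1 and T2; no exercise effect; two-sided 5%.

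**2. Visit-only test within the exercise arm.** The statistic is F = [SS_visit/(k−1)] / [SS_error/((n−1)(k−1))]. With k = 3 and n = 18 the degrees of freedom are 2 and 34, and the critical value is 3.28. For visit means (0, δ, δ) the squared deviations sum to (2/3)δ², so the noncentrality is λ = 18 × (2/3)δ²/(1−ρ) = 12δ²/(1−ρ). For δ = 0.5 and ρ = 0.5, λ = 12 × 0.25/0.5 = 6, and the test rejects in 54.4% of trials. The table sets this closed form beside a simulation of 6,000 trials per setting.

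| ρ | δ | λ | Visit-only, closed form | Visit-only, simulated | Arm-by-visit F | t-test on change | t-test on week 12 |
|---|---|---|---|---|---|---|---|
| 0.5 | 0.25 | 1.5 | 16.7% | 16.9% | 4.8% | 4.6% | 5.3% |
| 0.5 | 0.50 | 6.0 | 54.4% | 54.0% | 5.2% | 5.0% | 4.7% |
| 0.5 | 0.75 | 13.5 | 89.2% | 90.2% | 4.6% | 5.0% | 5.4% |
| 0.7 | 0.25 | 2.5 | 25.3% | 26.0% | 5.0% | 4.9% | 4.7% |
| 0.7 | 0.50 | 10.0 | 77.8% | 78.6% | 5.4% | 5.1% | 5.0% |
| 0.7 | 0.75 | 22.5 | 98.7% | 98.8% | 4.8% | 5.6% | 4.8% |

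With no shift, the visit-only test rejects in 5.0% (ρ = 0.5) and 5.6% (ρ = 0.7) of simulated trials. Pooling the arms makes matters worse: at ρ = 0.5 the simulated rates are 31%, 87% and almost 100%. The between-arm tests hold their level because the common shift cancels: δ − δ = 0.

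**3. Use of baseline.** With unit variance at each visit, the outcome variance per person entering the arm comparison is 1 for week-12 values, 2(1−ρ) for change, and 1−ρ² after adjustment for T0. At ρ = 0.5 these are 1, 1 and 0.75; at ρ = 0.7 they are 1, 0.60 and 0.51. Both unadjusted choices are valid, but each discards information already collected.

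**4. Regression to the mean, functional outcomes only.** Suppose frail entrants were all drawn from the lowest fifth of one measure with test-retest reliability R. Their mean T0 value would be −0.280/0.2 = −1.40 SD, and the expected untreated gain (1−R) × 1.40 = 0.42, 0.28 or 0.14 SD for R = 0.7, 0.8 or 0.9. Entrants from the other four fifths have a mean of 0.280/0.8 = 0.35 SD and an expected decline of 0.105, 0.07 or 0.035 SD. The frail-side figures are upper-end values. Frailty needs any three of five components, so many frail entrants will not be low on a given measure.

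**The case against.** The best reply is that the plan does compare the arms. The sentence just before the ANOVA gives a t-test or Mann-Whitney test between groups, and because the outcomes are defined as changes, the variables compared could well be changes. Step 2 shows that such a test is immune to shared drift. It is equally immune to regression to the mean, which randomisation balances between arms within a frailty group. This stands. It rules out saying that the trial has no valid between-arm test. It does not supply what is missing, since the sentence names neither 12 weeks nor change, and the article also uses the word group for frailty categories.

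A reader might go further and infer that drift will be reported as an exercise effect, or that efficacy will be claimed when the exercise arm is significant and the control arm is not. That rule would perform badly: in the simulation it gives a false positive in up to 24% of null trials. But the document neither proposes it nor calls the ANOVA or Friedman test the efficacy analysis. The text supports a risk of misreading, not a declared intention.

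Two other inferences go too far. One is that regression to the mean distorts the primary outcome, when frailty groups are not formed on cytokines. The other is that reagent lot is confounded with visit because, for the cultures, "The cells will be kept for 24 h". The article says nothing about lots, supernatants are stored frozen and could be assayed together, and staggered enrolment would make visits overlap in calendar time.

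Finally, an analysis plan that is not shown may hold more detail, including post-hoc contrasts between visits. That excuses silence. It does not excuse a stated test that cannot answer the question, because a fuller plan would have to replace this sentence, not just add to it.

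**Conclusion.** The point holds in a limited form. The stated longitudinal test has no arm factor and cannot separate exercise from change common to both arms. The stated between-arm test would be sound on 12-week values or change, but is fixed on neither and ignores baseline. No stated analysis is therefore fixed on the between-arm difference in 12-week change, which is what the primary outcome concerns.

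The size of the problem depends on shared drift, which the document does not quantify. Across the assumed range, the visit-only test rejects in roughly 17% to 99% of trials with no exercise effect, against about 5% for any of the between-arm tests. These rates describe what the visit-only test would do if it were read as evidence of efficacy. They do not predict the trial's error rate.

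**What to change.** Replace the ANOVA/Friedman sentence with wording such as: *Outcomes at 12 and 24 weeks are compared between arms with a linear mixed model containing arm, visit (12 or 24 weeks), arm-by-visit, the T0 value and frailty stratum, with participant as a random effect. Cytokines are analysed on the log scale where skewed. T0 enters as a covariate only and is not a level of visit. The arm difference at 12 weeks is the contrast of interest; the difference at 24 weeks is secondary. Any difference in effect by frailty status is assessed with an arm-by-frailty term. Within-arm changes over time are descriptive and are not evidence of efficacy.*

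If the t-test/Mann-Whitney sentence is kept, it should say which variables and which visit it applies to, and that it supports the model.

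The cost is slightly more analysis work, and within-arm P-values can no longer carry an efficacy claim. R is already named as software, the baseline and follow-up values are already scheduled, and neither recruitment nor measurement changes.
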